## Method/design

### Study design

This study is a randomized controlled parallel-group experiment with two conditions and two arms in the intervention condition. Participants are randomly assigned to either the control condition or the intervention condition. Participants in the intervention condition receive both the cognitive and behavioral module, but in different sequences. Specifically, participants in the intervention condition follow either first the cognitive and then the behavioral module (first treatment arm) or the reverse sequence (second treatment arm). In order to minimize contamination between the cognitive and behavioral module, individual participants in the intervention condition are not randomly assigned to a training sequence. Participants in the intervention condition from the same location (i.e. school) who start with the training at the same time (i.e. wave) follow the same sequence. In successive waves at the same school, the sequence will be reversed. An overview of the study design is presented in Fig. 1. Ethical approval for this study was granted by an independent medical ethics committee of the University Medical Center Utrecht.

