### Sample size

The sample size of this study is based on the expected difference on the primary outcome variables (emotion regulation and externalizing behavior problems) between the intervention condition (both sequences together) and the control condition. Meta-analyses demonstrated that the expected effect size (*d*) of cognitive behavioral therapy for children and adolescents with externalizing behavior problems is between 0.25 and 0.30 [5, 6]. To detect a small to medium effect (Cohen’s *d* = 0.25–0.30), with a two-sided type I error rate of 0.05, a power of 0.95, and three measurement moments, we will need between 100 and 142 participants [36]. To account for dropout, we have determined the total sample size to be 160 (80 participants in the control condition and 80 participants in the intervention condition).

Because previous research did not investigate differences between cognitive and behavioral training modules, it is not possible to estimate the expected effect size for the difference between modules. However, a sensitivity-power analyses showed that with 80 participants in the two intervention arms, an error rate of 0.05, a power of 0.95, and 19 repeated weekly measurements, even small effect sizes of 0.09 can be demonstrated with within-subjects analyses [36].

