**Fig. 2 Fig2:**
[figure not shown]
Spirit diagram. *Note. CAU* Care as Usual

If participants meet the inclusion criteria, they are randomly assigned to either the intervention or the control condition. Randomization takes place at the individual level, by means of computer-generated random numbers. Adolescents, their parents and teachers will obviously notice the condition in which they are participating, so allocation will not be blind. Nevertheless, participants will not be aware of the fact that we examine the difference between two training sequences. Subsequently, adolescent download a questionnaire application on their smartphone and start with the weekly and daily questionnaires. First, a 3-week baseline of the weekly measure (see measures section) will be established. Moreover, adolescents fill in the first Daily Diary measure on five consecutive days. In addition, adolescents, their parents and teachers complete the baseline measures at T1, the first of three assessments. The adolescent questionnaires and tasks are administered individually at school by a trained research assistant at each assessment point. Adolescents fill out the questionnaires on a computer. Teachers fill out the questionnaires on paper. Parents are sent links to the questionnaires via email.

Participants in the intervention condition start with either the cognitive module (Think Cool) or the behavioral module (Act Cool). After 5 weeks, in which participants in the intervention condition follow five individual therapy sessions, all participants, parents and teachers complete the T2 measures. Next, there is a 3-week training break, which allows us to measure possible delayed effects. During the training break, all participants continue to fill in the weekly questionnaire and fill in the second Daily Diary measure. Subsequently, participants in the intervention condition follow the second module (Think Cool or Act Cool, depending on the first module), which also consists of five individual sessions. Eventually, the post-test measures are completed by all participants at T3. There also is a 3-week post-measure of the weekly measure, in which participants also complete the third Daily Diary measure.

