### Analyses

Data will be analyzed according to the intention-to-treat principle [63], with multiple imputation as technique to handle missing data. To answer the first research question, whether the Think Cool Act Cool emotion regulation training is effective in enhancing emotion regulation skills and decreasing externalizing behavior problems, data of T1-T3 will be analyzed with analysis of variance and/or structural equation modeling. We will examine whether different aspects of emotion regulation and multi-informant perspectives of externalizing behaviors problems can be combined into latent variables. If this is the case, these latent variables will be used, in structural equation models. Otherwise, the analyses of variance will be conducted separately for the different constructs. To examine which module (Think Cool versus Act Cool) and which sequence most effectively increases emotion regulation capacities, we will use piecewise growth curve analyses and analysis of variance. Moderation will be tested by using multi-group analyses or regression analyses, and mediation will be tested with random-intercept cross-lagged panel models and parallel-process piecewise latent growth curve modeling. The analyses and reporting of results will be carried out according to the Consolidated Standards of Reporting Trials (CONSORT) [64].

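### Training sequence is alternated between whole school-waves with no stated random start, and the detectable effect for the module comparison makes no allowance for that clustering

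*Protocol article*

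**What the plan says.** All references are to the protocol article.

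- **Study design.** Within the intervention condition, "individual participants in the intervention condition are not randomly assigned to a training sequence". Trainees at one school "who start with the training at the same time (i.e. wave) follow the same sequence". Then: "In successive waves at the same school, the sequence will be reversed". The stated reason is to limit contamination between the two modules. How a school's first sequence is chosen is not described.
- **Procedure and randomization.** The random draw concerns intervention versus control only: "Randomization takes place at the individual level, by means of computer-generated random numbers". Participants are not told that sequences are being compared. Nothing is said on this about schools, recruiters or clinicians.
- **Analyses.** For the module and sequence questions, "we will use piecewise growth curve analyses and analysis of variance". No school, wave or other cluster term is named.
- **Sample size.** For the module comparison, the calculation takes the 80 trainees of both arms together, alpha 0.05 and power 0.95. Its conclusion is that with "19 repeated weekly measurements, even small effect sizes of 0.09 can be demonstrated with within-subjects analyses". No design effect is mentioned. The correlation between repeated measures and the metric of the 0.09 are not given.

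**The concern.** Separating the cognitive from the behavioral approach is the declared aim of the study, and the superiority of one module or one sequence is an explicit hypothesis. The arms that carry this contrast differ in how they were formed from the arms of the main comparison. Sequence belongs to a school-wave, not to an adolescent, and it is set by alternation.

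Three things follow.

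1. Once a school's first sequence is known, its next one is known before that wave consents and is screened.
2. Within a school, sequence coincides with calendar time. If most schools happened to start with the same module, that would hold across the whole trial.
3. The independent unit for the sequence contrast is the school-wave. Adolescents in one wave share a period and may share a trainer or teacher raters. If their outcomes, or their changes over time, are positively correlated for such reasons, an analysis that counts 80 independent adolescents gives intervals that are too narrow and a detectable effect that is too favourable.

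**Working it through.** **Step 1. Reproduce the plan's figure.** The inputs from Sample size are 80 trainees in two arms, 19 weekly measures, alpha 0.05 and power 0.95. The formula is repeated-measures ANOVA with a noncentral F under sphericity:

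λ = N·f²·m/(1−ρ), df1 = (k−1)(m−1), df2 = (N−k)(m−1), with k = 2 groups and m measures.

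The correlation ρ is not stated, so it was varied. The main comparison offers a cross-check, with f = d/2 and m = 3. There the article says "with a two-sided type I error rate of 0.05, a power of 0.95, and three measurement moments, we will need between 100 and 142 participants", for d of 0.30 and 0.25.

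| ρ | Detectable f (N = 80, m = 19) | N for d = 0.30 | N for d = 0.25 |
|---|---|---|---|
| 0.50 | 0.099 | 116 | 167 |
| 0.575 | 0.0915 | 99 | 142 |
| Article | 0.09 | 100 | 142 |

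One unstated correlation near 0.575 fits all three figures, with every participant treated as independent. That the 0.09 is Cohen's f is inferred from this fit.

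**Step 2. Design effect.** Cluster size and ICC are not in the document. Assume 4-8 trainees per school-wave (80/4 = 20 to 80/8 = 10 clusters) and an ICC of 0.05-0.10. Then DEFF = 1 + (m−1)·ICC, with m now the trainees per wave. Effective N is 80/DEFF, and the true error of a nominal 5% test is 2·[1 − Φ(1.96/√DEFF)].

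| Trainees per wave | ICC | DEFF | Effective N | True error |
|---|---|---|---|---|
| 4 | 0.05 | 1.15 | 70 | 6.8% |
| 4 | 0.10 | 1.30 | 62 | 8.6% |
| 8 | 0.05 | 1.35 | 59 | 9.2% |
| 8 | 0.10 | 1.70 | 47 | 13.3% |

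**Step 3. Allow for the reversal within schools.** The formula in step 2 ignores the fact that a school runs both sequences. A simulation of an ordinary t-test on sequence, with two waves per school and one wave per sequence, separates the two sources of clustering:

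| Layout | Variance between waves within school | Variance between schools | Type I error |
|---|---|---|---|
| 10 schools × 2 waves × 4 | 5% | 0 | 6.8% |
| 10 schools × 2 waves × 4 | 10% | 0 | 8.5% |
| 5 schools × 2 waves × 8 | 5% | 0 | 9.2% |
| 5 schools × 2 waves × 8 | 10% | 0 | 13.1% |
| 10 × 2 × 4 | 5% | 5% | 6.3% |
| 5 × 2 × 8 | 5% | 5% | 8.6% |
| 10 × 2 × 4 | 0 | 10% | 4.4% |
| 5 × 2 × 8 | 0 | 10% | 4.2% |

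The inflation comes from the wave-within-school part. Purely between-school variation cancels, and the test is then slightly conservative.

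**Step 4. Effect on the 0.09.** Put the effective N into the formula of step 1 (ρ = 0.575), as an approximation only. At N = 70 the detectable f is 0.098, and power at f = 0.0915 is 91%. At N = 50, near the lower end of the range, they are 0.116 and 75%. This carries over to the module contrast only as far as the correlation concerns change over time, because stable cluster differences drop out of a within-person contrast.

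**The case against.** Several points on the other side are sound.

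- **Allocating by wave has a good reason.** It limits contamination between modules, and the article openly discloses that sequence is not individually randomised. Both points stand. Neither requires the starting order to be left undrawn.
- **The article names model families only.** A growth model can carry a school-wave term, and an analysis plan that is not shown may add one. A reader might infer that the tests will certainly be run at individual level; the document does not say so. What the article does fix is the 0.09, which contains no allowance for clustering. A later plan also cannot make an alternation random.
- **Reversal within schools protects against stable school differences.** This stands, as step 3 shows. A reader might infer that the intervals are too narrow in any event, but that holds only with positive correlation within waves beyond the school level.
- **Every trainee receives both modules.** Stable cluster differences therefore cancel in the within-person module contrast. School-wave differences in change over a period do not.
- **Selection is limited.** A reader might infer that staff could steer chosen adolescents into a sequence. Schools write to all potentially eligible adolescents, entry depends on set cut-offs, and the draw between intervention and control comes after consent and screening. The next sequence is foreseeable, but the documents give no sign that this was exploited.
- **The main comparison is not touched.** The total sample size rests on intervention versus control, which is individually randomised. A reader might infer that this draw was unrestricted and left waves without concurrent controls; the article neither states nor excludes blocking.

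**Conclusion.** The point holds in a limited form. By the article's own description, sequence is allocated to school-waves by predictable alternation, and no random first choice is stated. The sequence comparison, and the module comparison that depends on it, are therefore non-randomised cluster comparisons tied to calendar time within each school. The 0.09 counts 80 independent participants.

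The size is conditional. It is about 7-13% true error for a nominal 5% test of sequence, if clustering is ignored, waves hold 4-8 trainees and an ICC of 0.05-0.10 lies wholly between waves within schools. It is about 4% if clustering is only between schools and each school runs both sequences equally. Neither cluster size nor ICC can be taken from the document.

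This should be fixed, because it bears on the study's declared aim. It is not a fault of the intervention-versus-control result.

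**What to change.** 1. Draw each school's starting sequence at random, balanced across schools. Conceal each wave's sequence from schools and recruiters until that wave is enrolled.
2. Include school-wave and period in the module and sequence models, with a small-cluster correction (small-sample degrees of freedom or a bias-corrected cluster-robust standard error).
3. Restate the 0.09 with its metric, the assumed correlation between repeated measures and a design effect over a stated range of cluster size and ICC.
4. Describe the sequence comparison as cluster-allocated, or as non-randomised if the starting order is not drawn.

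The cost is one random draw per school and some wording. Module and sequence intervals become somewhat wider and the detectable effect less favourable. No extra participants are required, and allocation by wave, with its protection against contamination, is kept.

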**Fig. 1 Fig1:**
[figure not shown]
Overview of study design

### Eligibility criteria

Participants are recruited from Dutch high schools. Participants are between 12 and 16 years old, with elevated levels of externalizing behavior problems. The following inclusion criteria will be used: a subclinical or clinical level of externalizing behavior problems as reported by teachers (TRF externalizing subscale >84th percentile) and average or above average intelligence (estimated IQ score > 80). Participants are excluded if they experience severe Autism Spectrum symptoms as reported by their teacher (ASV symptom score > 98th percentile) and/or if their language, auditory or visual skills are severely hindered (as evidenced by an indication of the school psychologist that the adolescent possesses insufficient Dutch language skills to understand questionnaires and training, or has an auditory or visual disability). Participants with mild Autism Spectrum symptoms (ASV symptom score < 98th percentile) and/or other comorbid psychiatric problems (e.g., depression, ADHD) are not excluded from participation in this study.

### Sample size

The sample size of this study is based on the expected difference on the primary outcome variables (emotion regulation and externalizing behavior problems) between the intervention condition (both sequences together) and the control condition. Meta-analyses demonstrated that the expected effect size (*d*) of cognitive behavioral therapy for children and adolescents with externalizing behavior problems is between 0.25 and 0.30 [5, 6]. To detect a small to medium effect (Cohen’s *d* = 0.25–0.30), with a two-sided type I error rate of 0.05, a power of 0.95, and three measurement moments, we will need between 100 and 142 participants [36]. To account for dropout, we have determined the total sample size to be 160 (80 participants in the control condition and 80 participants in the intervention condition).

Because previous research did not investigate differences between cognitive and behavioral training modules, it is not possible to estimate the expected effect size for the difference between modules. However, a sensitivity-power analyses showed that with 80 participants in the two intervention arms, an error rate of 0.05, a power of 0.95, and 19 repeated weekly measurements, even small effect sizes of 0.09 can be demonstrated with within-subjects analyses [36].

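### The stated 100–142 participants do not give 0.95 power at Cohen's d = 0.25–0.30; the figures match an effect twice that size, most likely because d was entered as Cohen's f

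*Protocol article*

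**What the plan says.** The Sample size section of the protocol article powers the contrast "between the intervention condition (both sequences together) and the control condition". The effect size is labelled as d twice: first from the literature ("Meta-analyses demonstrated that the expected effect size (*d*) of cognitive behavioral therapy" in "children and adolescents with externalizing behavior problems is between 0.25 and 0.30 [5, 6"), then as the planning value ("To detect a small to medium effect (Cohen’s *d* = 0.25–0.30"). The other inputs are given as "with a two-sided type I error rate of 0.05" and "a power of 0.95, and three measurement moments, we will need between 100 and 142 participants". The number is then rounded up: "To account for dropout, we have determined the total sample size to be 160", split equally, 80 and 80.

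The section does not name the test, gives no conversion from d to another effect-size scale, and gives no correlation among the three assessments. The Analyses section plans analysis of variance and/or structural equation modelling on T1–T3 for this question.

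**The concern.** A difference of a quarter to a third of a standard deviation between two groups normally needs several hundred participants for 0.95 power. Three correlated assessments reduce that number, but rarely to 100–142. ANOVA-based power calculations commonly take Cohen's f, and with two equal groups f is half of d. Entering d as f therefore doubles the assumed effect and cuts the required sample to about a quarter.

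This is the only sample-size justification for the first research question. A reader of the protocol would take the trial to have a 5% chance of missing an effect of the expected size. If the effect size was doubled by mistake, that chance is much larger.

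**Working it through.** **Inputs from the Sample size section:** two equal groups; m = 3 measurements; two-sided alpha 0.05; power 0.95; d = 0.25 and 0.30; stated N = 142 and 100; planned N = 160. **Assumption:** correlation ρ among the repeated measures, not stated; 0.5 as the base case, range 0 to 0.9.

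**1. Reproducing the stated N.** Between-factors test, repeated-measures ANOVA: noncentral F with 1 and N − 2 degrees of freedom and λ = N·m·f² / (1 + (m − 1)ρ). At ρ = 0.5 the denominator is 2.

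- f = 0.25, N = 142: λ = 142 × 3 × 0.0625 / 2 = 13.31, power 0.952. N = 140 gives 0.949, so 142 is the smallest even N.
- f = 0.30, N = 100: λ = 100 × 3 × 0.09 / 2 = 13.50, power 0.953. N = 98 gives 0.9496, so 100 is the smallest even N.

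Both ends of the stated range match exactly at one round correlation, with 0.25 and 0.30 on the f scale.

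**2. Converting d.** For two equal groups f = d/2, so d = 0.25 is f = 0.125 and d = 0.30 is f = 0.15. Read the other way, f = 0.25–0.30 is d = 0.50–0.60. N for 0.95 power in the same test:

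| ρ | d = 0.25 | d = 0.30 |
|---|---|---|
| 0 | 280 | 196 |
| 0.5 | 558 | 388 |
| 0.9 | 780 | 542 |

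No correlation from 0 to 0.9 brings this test to 142 and 100.

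**3. Power at the stated d, same test.** Example: N = 142, d = 0.25, ρ = 0.5 gives λ = 142 × 3 × 0.015625 / 2 = 3.33, power 0.44.

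| N | ρ | d = 0.25 | d = 0.30 |
|---|---|---|---|
| 142 | 0.5 | 0.44 | 0.59 |
| 160 | 0 | 0.78 | 0.90 |
| 160 | 0.5 | 0.49 | 0.64 |
| 160 | 0.7 | 0.42 | 0.56 |
| 160 | 0.9 | 0.37 | 0.50 |

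N = 142 corresponds to losing 18 of 160, about 11%.

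**4. Other analyses of T1–T3 at N = 160.**

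- Group-by-time test with group differences 0, d, d at T1, T2, T3. The centred pattern gives f = d/(3√2), that is 0.059 and 0.071. With λ = N·m·f² / (1 − ρ) and ρ = 0.5, λ = 3.33 and 4.80 on 2 and 316 degrees of freedom: power 0.35 and 0.48.
- Mean of T2 and T3 adjusted for T1. Residual variance is (1 + ρ)/2 − ρ², that is 0.50, 0.36 and 0.26 at ρ = 0.5, 0.7 and 0.8. Power for d = 0.25 and 0.30 is 0.60 and 0.76, then 0.75 and 0.88, then 0.87 and 0.96.

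Across these two analyses at the correlations shown, only d = 0.30 with ρ about 0.8 and no dropout reaches 0.95.

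**The case against.** **The mechanism is a reconstruction.** The protocol shows neither an f input nor a correlation, and there is another route to the same numbers. A group-by-time interaction with correctly converted f = d/2 and ρ = 0.575 also gives 142 and 100. A group-by-time test is a natural reading of a design with three assessments. This stands as a reason to call the d-for-f mix-up most likely rather than certain. It does not rescue the stated power. At ρ = 0.5 that route gives 168 and 116, so it needs a correlation tuned to 0.575. Moreover, f = d/2 is too large for that interaction when the groups do not differ at T1, which precedes training; with differences 0, d, d the power is the 0.35–0.48 shown above.

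**A reader might infer that 0.64 is the most the trial can achieve.** The documents do not support that. The correlation is unstated, the same test gives 0.78–0.90 at ρ = 0, and a baseline-adjusted analysis gives more than 0.64 over much of the range. The Analyses section leaves room for such models.

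**A reader might also infer much lower power,** because the reproduced test averages in T1, where no effect is possible. With differences 0, d/2, d or 0, d, d and ρ = 0.5, that averaged test would have power of 0.15–0.31 at N = 142. But the protocol does not commit to testing a group main effect over all three assessments, so this is not the trial's power.

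**Nor does the protocol say that a non-significant result will be read as absence of effect.** It commits to CONSORT reporting. The fault is in the stated power, not in a declared rule of interpretation.

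**Conclusion.** The point holds in this form: 100–142 participants do not follow from d = 0.25–0.30 with 0.95 power in the between-groups model that reproduces them. The most likely explanation is that d was entered as f, in which case the 0.95 applies to d = 0.50–0.60. Under that model at ρ = 0.5, the required N is 558 and 388, roughly four times the stated figures. The chance of missing the expected effect is about 36–51% with 160 participants (1 − 0.637 to 1 − 0.486) and about 41–56% with 142, instead of 5%.

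These sizes rest on equal groups, compound symmetry and an assumed ρ. Over ρ = 0 to 0.9 the same test has power between 0.37 and 0.90 at N = 160, always short of 0.95. A condensed article may leave out the test and the correlation. The issue is that the effect size, power and sample size it does state do not agree.

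**What to change.** Leave enrolment at 160 and correct the Sample size section:

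1. Check the original calculation and state the test, the effect-size metric and the correlation actually used. These should come from the investigators' records, not from the reconstruction above.
2. If f was entered, relabel the effect as d = 0.50–0.60; otherwise correct the stated power.
3. Restate power at d = 0.25–0.30, and the detectable difference, for 142–160 participants over a range of correlations and for the analysis that will be used. As an example, a T3 comparison adjusted for T1 with N = 142 and ρ = 0.5–0.7 detects about d = 0.34–0.41 at 80% power and 0.44–0.53 at 95%.

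The cost is a few sentences and a less favourable stated power. No additional participants and no change to the intervention are needed.
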